## Abstract

**Background:**

Depression is a highly prevalent mental disorder with major public health effects globally. It impairs the quality of life and reduces the ability to work and function, leading to increasing costs of sick leaves and disability pensions. Current treatment strategies focus on biological and psychological pathways while understating the role of lifestyle factors. Epidemiological studies have shown convincing evidence of an inverse relationship between diet quality and depression. However, only limited data are available on the therapeutic effects of diet quality improvement on depression. Using a randomized controlled trial design, our primary aim is to investigate the effectiveness and cost-effectiveness of a behavioral nutrition group intervention compared to a social support intervention in the treatment of depression.

**Methods:**

Participants (*N*=144, aged 20–65 years) with a diagnosis of moderate or severe depression recruited in collaboration with outpatient care units will be randomized into two arms: Food for Mind (FM) nutrition intervention (*n*=72) or Bring Good Mood (BGM) social support control group (*n*=72). Both arms will be provided with 6 group sessions over an 8-week period. FM involves improving diet quality by applying strength-based behavioral nutrition counseling and activities facilitated by a registered dietitian. The control arm comprises a befriending protocol. During the interventions, all participants will continue their treatment for depression as usual. Longitudinal data are collected at baseline, at 8 weeks, and at 6- and 12-month follow-ups. Depressive symptoms, diet quality, eating behavior, ability to work and function, and quality of life are assessed by self-reported questionnaires. A treatment expectancy questionnaire will be administered at baseline and an acceptability questionnaire at 8 weeks. The Center for Epidemiologic Studies Depression Scale is used as the primary endpoint at 1 year. The results will be analyzed with linear mixed-effects models. Economic evaluation includes both cost-effectiveness and cost-utility analysis. Two incremental cost-effectiveness ratios will be calculated to evaluate the incremental cost per QALY and the incremental cost per improvement in CES-D.

**Discussion:**

If the intervention proves to be cost-effective and acceptable, it be can be implemented in healthcare to support the treatment of depression.

**Trial registration:**

ClinicalTrials.gov NCT03904771. Retrospectively registered on 5 April 2019

**Supplementary Information:**

The online version contains supplementary material available at 10.1186/s13063-021-05279-5.

## Administrative information

Note: the numbers in curly brackets in this protocol refer to SPIRIT checklist item numbers. The order of the items has been modified to group similar items (see http://www.equator-network.org/reporting-guidelines/spirit-2013-statement-defining-standard-protocol-items-for-clinical-trials/).

## Introduction

### Background and rationale {6a}

Depression is a globally prevalent illness affecting approximately 250 million people around the world [1]. Depression causes a significant decrease in a person’s work ability and functional capacity [2–4] and also impairs the person’s quality of life [5–7]. Depression is associated with obesity [8]. In addition, the adverse effects caused by some antidepressant drugs, such as mirtazapine, are associated with a high risk of inducing weight gain [9, 10]. The economic burden caused by depression is substantial [11]. Depression is already a leading cause of disability in Europe [12] and is expected to become the leading cause of disability worldwide by 2030 [13].

According to evidence-based clinical guidelines [14, 15], depression is mainly treated with pharmacotherapy and psychotherapy. The treatment as usual seems to be effective in only one out of three cases [16, 17]. Moreover, depression is often recurrent, with relapses in at least 50% of the cases [18, 19]. It is noteworthy that the potential adverse effects associated with some antidepressants, such as weight gain, can reduce adherence to medication. In addition to the treatment as usual, the International Society for Nutritional Psychiatry Research advocates for the recognition of nutrition as an essential part of the rehabilitation of depression, as nutrition also supports the somatic well-being of patients with depression [20]. A decision on treatment should not be based solely on clinical efficacy, but on a combination of clinical efficacy and cost-effectiveness. Although there is little evidence of the financial benefits brought by a dietary intervention for treating depression, there are two recently published studies on the matter. One of them indicated that dietary treatment was highly cost-effective in treating major depression compared to a social support group program [21], while the other produced the same amount of QALYs with lower costs [22].

Despite the evidence-based association between nutrition and depression in epidemiological studies [23], the role of nutrition in the treatment of depression has thus far been primarily limited to weight management.

The benefits of the Mediterranean diet to reducing the risk of depression were already investigated in 2013 [24]. Recent reviews and meta-analyses have shown a significant association between overall diet quality and a lower risk of depression and less severe symptoms of depression [23, 25]. Such diets are high in vegetables, fruit, whole grains, seeds, nuts, and fish, while containing a limited amount of processed foods. A significant inverse association between adherence to the Mediterranean diet and the probability of depression was found in an analysis of cross-sectional studies [26], and according to the most recent meta-analysis, an improvement in diet quality can significantly reduce the symptoms of depression [27].

So far, only two randomized controlled trials have been conducted to evaluate the impact of nutrition counseling in patients who have been diagnosed with depression. The SMILES trial was the first clinical study to show that individualized nutritional counseling (7 × 1h) significantly improved diet quality, alleviated the degree of depression, increased the remission rate compared to the control group, and was feasible [28]. In the HELFIMED study, a 3-month group-based Mediterranean-style diet intervention, healthy dietary changes supplemented with fish oil were found to be beneficial for treating depressive symptoms [29]. In the same study, the intervention group participating in cooking workshops was cost-effective compared to a social support group [21].

The few previous studies have placed their focus on the impact of a dietary change on depressive symptoms. Less emphasis has been put on the mechanisms underlying a behavioral change, although other areas of research have increasingly recognized, the importance of lifestyle changes, the role of the behavior change theory, and related techniques [30].

In the Food for Mind study presented here, behavioral nutrition counseling utilizes a strength-based counseling approach, which is based on positive psychology [31] and self-determination theory (SDT) [32], and applies counseling techniques from motivational interviewing (MI) [33] and solution-focused therapy (SFT). These theories and therapeutical methods share a person-centered approach to supporting individual agency. They are described in more detail in the methods section.

## Objectives {7}

The aim of the Food for Mind study is to examine the effects of a strength-based nutrition group intervention on the symptoms of depression, diet quality, eating habits, quality of life, and work ability in patients diagnosed with depression and to evaluate its cost-effectiveness when implemented in a health care system.

The following is the primary objective:
To explore the effectiveness of the strength-based Food for Mind group intervention for alleviating the symptoms of depression

The following are the secondary objectives:
To explore whether the strength-based Food for Mind group intervention improves diet quality, eating competence, quality of life, and work abilityTo evaluate the cost-effectiveness of the strength-based Food for Mind group intervention compared to a control group

## Trial design {8}

This study is a two-parallel group, randomized controlled clinical trial exploring the effects of a strength-based nutrition group intervention in patients diagnosed with depression. In this trial with a subject allocation ratio of 1:1, the Food for Mind intervention is expected to be superior to a social support group as a standalone intervention. The protocol is outlined in Fig. 1, and details of the assessments are given in Table 2.

**Fig. 1 Fig1:**
[figure not shown]
Schematic diagram of the study procedures

## Methods: participants, interventions and outcomes

### Study setting {9}

The study will be carried out at the Institute of Public Health and Clinical Nutrition at the University of Eastern Finland in Kuopio, Finland.

### Eligibility criteria {10}

#### Inclusion criteria

Male and female participants will be eligible if they (1) are aged between 20 and 65 years, (2) have the ICD-10 diagnosis of depression (F32.1, F32.2, F32.8, F32.9, F33.1, F33.2, F33.8, F33.9, or F34.1), (3) have an individually tailored treatment and rehabilitation plan in an outpatient treatment unit, (4) are receiving treatment (medication and/or psychotherapy) that has remained unchanged for at least 2 weeks prior to randomization, and (5) are willing to participate in a group-based intervention for 8 weeks including 6 group sessions.

#### Exclusion criteria

Participants will be excluded if they (1) have a medical illness that is clinically unstable and which could be aggravated by the intervention, (2) are pregnant, (3) are participating in another nutrition or exercise intervention, and (4) have a current depressive episode or recurrent depressive disorder that is severe with psychotic features, a personality disorder, a severe eating disorder, and/or a substance abuse disorder.

### Who will take informed consent? {26a}

All participants will be recruited by a research dietitian after the informed consent process. The research dietitian will send the study description statement to eligible participants by post or email to provide potential participants with information before meeting the research dietitian. In the meeting, the research dietitian will give an informed consent form to the participants and explain this to them. The informed consent form is signed by the participants and the research dietitian. The participants have a right to withdraw from the study at any time during the research process.

### Additional consent provisions for collection and use of participant data and biological specimens {26b}

Not applicable; specimens were not collected.

### Interventions

#### Explanation for the choice of comparators {6b}

Social support is known to alleviate depressive symptoms [34]. As the Food for Mind intervention also includes a social dimension, the group will be standardized with a social support control group.

#### Intervention description {11a}

Both the FM intervention groups and the BGM control (befriending) groups meet 6 times (5 1.5-h sessions and 1 3-h session) over an 8-week period. Each group has 6 to 8 participants. For social peer support, both groups will have their own WhatsApp groups, in which participants can share their own experiences and findings. The WhatsApp mobile application is used during the intervention and for the subsequent 10 months. Both groups continue their usual treatment for depression (treatment as usual) during the study.

A written manuscript prepared for every FM group meeting drawn up together in collaboration with a behavioral scientist helps the research dietitian to stick to a cohesive plan when instructing the group. The implementation of the BGM group meetings is also harmonized by the same instructor.

#### Intervention group

The primary focus of the behavioral nutrition counseling is on improving diet quality based on the “Food for Health” Finnish Nutrition and Food Recommendations [35]. According to these recommendations, a health-promoting diet focuses on the consumption of vegetables, fruit and berries, whole-grain products, legumes, fish, vegetable oils and vegetable oil-based spreads, nuts and seeds, and fat-free or low-fat dairy products. Its composition is illustrated by the food pyramid design and single meals by the plate model. A high-quality diet has a low energy density, encompasses a need for all nutrients, and contains plenty of bioactive compounds [35]. In addition to nutritional quality, emphasis is placed on a regular meal rhythm set by breakfast, lunch, and dinner and one or two snacks as needed [35].

Behavioral nutrition counseling utilizes a strength-based counseling approach, which is based on equality and a patient-centered approach [36]. Positive psychology has identified several mechanisms that can boost health behavior, including the identification of the individual’s existing strengths increasing self-efficacy and positive affect. Learning positive thinking and applying a solution-focused rather than problem-focused approach helps finding more solutions, has direct effects on immediate mental well-being, and strengthens psychological vantage resources. Positive affect during health behavior enables enjoyment and appreciation of the process instead of just its outcome. It builds the individual’s resources and strengthens unconscious motives [31].

According to SDT, a theory of motivation and personality, people are motivated to grow and change when their universal basic psychological needs for autonomy, competence, and relatedness are fulfilled. SDT sees motivation as a continuum from the intrinsic to the extrinsic, intrinsic motivation leading to more permanent achievements. Intrinsic motivation is enhanced by reinforcing innate needs for the senses of autonomy, competence, and relatedness [37]. MI provides some useful techniques that are in line with the SDT. The most important element of MI is its collaborative, appreciative spirit that aims to understand the patient and establish rapport with her/him [38].

SFT focuses on the present circumstances, desired future, possibilities, goals, progress, and strengths [39]. The person’s sense of autonomy is enhanced by placing the responsibility for a change in the hands of individuals by giving them an opportunity to choose and set their own goals and the means used to achieve these goals. Paying attention to the individual’s skills and potential increases his/her sense of competence, and this combined with respectful and patient-centered empowering language enhances feelings of relatedness.

By utilizing basic counseling skills, including presence and listening, genuineness, empathy, positive regard, and reflection, a counselor promotes the client’s motivation, readiness, willingness, and ability to take more responsibility for his/her personal well-being and improving dietary habits.

The topic of each of the six group meetings, including activities, assignments, and actions aiming to enhance the participants’ sense of autonomy, competence, and relatedness, is described in Table 1. In summary, each meeting includes discussions on the topic of the session; action-based methods, such as grocery shopping, cooking, eating together, and using all senses; and completing home assignments aiming to elucidate how the participants can improve their diet quality in their daily lives in practice. Each new meeting starts with the participants providing feedback on their experiences and positive changes, if any, in their eating habits resulting from completing the home assignments. In each group meeting, participants receive printed counseling material and assignments related to the day’s topic. The material and assignments aim to support the group participants to observe their eating behavior and practice mindful eating to identify hunger and satiety and pinpoint how they are feeling. The intervention group sessions are facilitated by the research dietitian. The protocol of each nutrition counseling meeting is presented in Additional file 1 (see Additional file 1).

**Table 1 Tab1:** Activities, assignments, and actions to enhance participants’ sense of autonomy, competence, and relatedness

Meeting topics and learning objectives (LO)	Activities	Home (HA) and WhatsApp (WA) assignments	Sample actions to enhance the sense of autonomy, competence, and relatedness
1. Getting to know each other: - Grouping - Finding strengths LO: “We’ll get to know each other, and I feel like I’m an important part of the group.”	1. Finding personal strengths 2. Sharing thoughts of personal motives to participate in the FM group Group discussion: nutrition and depression—how eating affects your mood	HA: keeping a record of health-promoting eating habits during good and bad days WA: sharing a photograph of one personally meaningful thing	Autonomy: finding out the participants’ important/meaningful reasons/motives for participating Competence: identifying existing knowledge of the topic Relatedness: noticing and respecting individual experiences, giving and receiving social support
2. Diet quality and meal frequency: - Identifying health-promoting characteristics in diet - Setting realistic goals LO: “I’ll understand the meaning of meal rhythm and diet quality to my wellbeing.”	1. Experiences of differences in diet and eating between good days and bad days 2. Goal setting	HA: focusing on meal frequency for a week HA: evaluation of ones’ own eating patterns WA: sharing favorite starter, main dish, and dessert chosen from the Food for Mind—recipe booklet	Autonomy: encouraging/helping participants to choose and set realistic and meaningful goals of their own and to plan actions that they will be committed to in achieving them. Competence: noticing and strengthening what is already good in the participants’ current habits and helping them plan concrete actions leading them to achieve their goals Relatedness: respecting differences in the participants’ habits and experiences, making use of this diversity when promoting change, giving and receiving social support
3. Nutrition and depression—evidence-based knowledge: - Identifying existing positive characteristics in meal frequency and eating habits LO: “I’ll understand evidence-based knowledge about the association between depression and diet/nutrition.”	1. Experiences and findings about meal frequency and its effects on good mood—discussion in pairs and in group Group discussion: nutrition and depression utilizing evaluations of participants’ own eating patterns	HA: adding one food item known to affect depression positively to your diet HA: getting familiar with mindful eating WA: participants sharing a picture of a food item or a dining experience, which has made them feel good	Autonomy: introducing several options of food items with a positive effect on depression and offering the participants freedom of choice Competence: noticing and strengthening the factors already good in the participants’ current habits and helping them make sustainable choices for new habits Relatedness. utilizing team/groupwork to enhance team spirit and to give and receive social support
4. Food for Mind in practice: - Practicing mind-friendly cooking - Familiarization with mindful eating LO: “I’ll learn to prepare easy and mind-friendly food.”	1. Group exercise about mindful eating and different hunger types using a mind map 2. Cooking, utilizing mindfulness 3. Eating together applying mindful eating	HA: existing food choices in the participants’ diet WA: sharing a photograph of a situation, in which a participant has utilized or could utilize mindfulness in the future	Autonomy: creating an atmosphere that supports participants’ sense of autonomy Competence: training on new skills (new cooking skills), strengthening existing (cooking) skills Relatedness: utilizing team/groupwork to enhance team spirit and to give and receive social support
5. Food for Mind food items in a grocery store—navigation: - Getting familiar with a mind-friendly food selection LO: “I’ll get new tips to my food choices.”	1. The participants’ experiences and observations of their own food choices 2. Getting familiar with the selection of Food for Mind food items available in the grocery store	HA: focusing on meal frequency for a week WA: sharing a photograph of one mind-friendly food item each participant has adopted in diet	Autonomy: learning to read labels to make personally relevant and acceptable choices Competence: giving positive feedback about what is already good in the participants’ current food choices, learning to read and understand labels, and using this knowledge in one’s daily life Relatedness: utilizing pair/team/groupwork to enhance team spirit and to give and receive social support
6. Tools for the future: - Discovering and ensuring to the tools the participants have for putting the dietary goals into action and successfully maintaining them LO: “I’ll notice my success and I’ll find ways to enhance my mood.”	1. A gallery walk-through method for group success, benefits, support, and future prospects with group discussion 2. Group discussion: hopefulness and gratefulness	Future exercises - Gratefulness exercise - Letter for the future exercise	Autonomy: highlighting the active and autonomous role participants have played in selecting and making lifestyle choices that have improved their health and well-being Competence: positive feedback on personal and group success Relatedness: giving and receiving social support

#### Control group

The BGM control group follows a befriending protocol [34] and has a visit schedule identical in its content and length with the FM intervention group. The befriending group consists of a discussion of neutral topics of interest, such as hobbies, music, and sports, and engaging in activities together, with the intention of keeping participants engaged and in a positive mood. Befriending groups are facilitated by a rehabilitation counselor from a non-profit association (Turvalinkki ry), which organizes activities open for anyone with a focus on considering the needs and wishes of mental illness rehabilitees.

### Criteria for discontinuing or modifying allocated interventions {11b}

There will be no special criteria for discontinuing or modifying allocated interventions.

### Strategies to improve adherence to interventions {11c}

Diet quality is assessed with the Index of Diet Quality and Diet Frequency Questionnaire at the baseline, at the end of the intervention, at the 6-month follow-up, and at the end of the study (12-month follow-up) to monitor the adherence with the intervention.

### Relevant concomitant care permitted or prohibited during the trial {11d}

All participants will receive treatment as usual as part of their psychiatric treatment unaffected by this study or the group in which they participate.

### Provisions for post-trial care {30}

At the end of the study, the participants in the BGM group will receive the same Food for Mind nutrition counseling material as the participants in the FM group, and they have an opportunity to participate in one depression and nutrition group session (1.5 h) facilitated by the research dietitian.

### Outcomes {12}

#### Primary outcomes

The primary outcome (depression) is a change in the CES-D Depression Scale [40] scores from the baseline to the 12-month follow-up.

A clinically relevant change is defined as (a) an at least 50% decrease in the CES-D Depression Scale score and (b) a total score undercutting certain limit values. In addition to the typical cutoff score of 16, cutoff points of 12 [41] and 22 [42] are used in the analysis.

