#### Follow-up outcomes

Follow-up outcomes are changes in the primary and secondary outcomes from baseline to the 8-week and 6-month follow-up.

Other pre-specified outcomes are as follows:
Treatment expectancy questionnaire: As treatment expectations may influence the outcome, they will be evaluated with the treatment expectancy questionnaire [51] and taken into account in the statistical analysis.Acceptability: The acceptability of the Food for Mind group rehabilitation program will be evaluated with the acceptability questionnaire based on the Theoretical Framework of Acceptability (TFA) [52].Changes in weight, body mass index (BMI), body fat, and fat-free body mass as measured with a body composition analyzer (InBody 720) from baseline to 12 months.

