### Sample size {14}

The total sample size of *n*=144 is based on the power calculation, when *α*=0.05, power=0.8, and effect size=0.5, and the estimated loss of participants is 15%. The calculation is based on the decline of 7 points assessed with the Center for Epidemiologic Studies Depression (CES-D) Scale.

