## Statistical methods

### Statistical methods for primary and secondary outcomes {20a}

The effects of the intervention on the primary and secondary outcomes will be analyzed following the intention-to-treat (ITT) principle. Group differences will be estimated using linear mixed effects models which allow considering the nested dependency structure generated from small groups and small group counselors in the data. All tests will be conducted using an alpha level of 0.05 and reporting 95% confidence intervals. Statistical analysis will be performed using the R software [72] and IBM SPSS Statistics® (IBM Corp., Armonk, NY, USA).

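### The outcomes are defined as change from baseline and no adjustment for the baseline value is stated; adjusting the 12-month CES-D comparison for baseline CES-D would gain precision at no cost

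*Protocol article*

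**What the plan says.** Under Primary outcomes the protocol article states: "The primary outcome (depression) is a change in the CES-D Depression Scale [40] scores from the baseline to the 12-month follow-up". The Secondary outcomes section uses the same form, change from baseline to 12 months, for IDQ, ecSI 2.0, TFEQ-R18, AQoL-8D and work ability. The Follow-up outcomes section uses it for 8 weeks and 6 months. The abstract is worded differently and does not mention change: "The Center for Epidemiologic Studies Depression Scale is used as the primary endpoint at 1 year".

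The analysis is given in Statistical methods {20a}: "Group differences will be estimated using linear mixed effects models which allow considering the nested dependency structure generated from small groups and small group counselors". That section does not say whether the response is the change or the repeated scores, or how the baseline value enters. The only adjustment variable named anywhere is treatment expectancy, of which the Follow-up outcomes section says "they will be evaluated with the treatment expectancy questionnaire [51] and taken into account in the statistical analysis".

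Baseline CES-D will be available. Table 2 lists CES-D at baseline, 8 weeks, 6 months and 12 months, and Concealment mechanism {16b} places the baseline assessments before randomisation.

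**The concern.** Read together, the outcome definitions and the model description lead to a between-arm difference in mean change. Naming a mixed model does not alter this. If baseline is part of the response and each arm has its own free baseline mean, the group-by-time contrast at 12 months equals, with complete data, the difference in mean change.

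A change score subtracts the whole baseline value, whereas the best predictor of the 12-month score uses only a fraction of it. The excess adds noise. Precision matters here because the trial is sized close to its power target, and Sample size {14} mentions no allowance for the small-group dependency that the analysis expects.

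**Working it through.** **1. The plan's own figure.** Sample size {14} gives alpha 0.05, power 0.8, effect size 0.5, 15% loss and a total of 144. It adds: "The calculation is based on the decline of 7 points assessed with the Center for Epidemiologic Studies Depression (CES-D) Scale". A 7-point difference at effect size 0.5 implies an SD of 7/0.5 = 14. By the two-sided normal approximation:

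- n per arm = 2 × (1.96 + 0.84)² / 0.5² ≈ 63, so 126 in total.
- 126 × 1.15 = 144.9, which matches the stated 144 to within rounding.
- With 15% loss, 72 × 0.85 ≈ 61 completers per arm. Power = Φ(7 / (14 × √(2/61)) − 1.96) = 78.9%.

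The article does not say whether 14 is the SD of a score or of a change.

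**2. Variance of the two estimators.** Let σ² be the CES-D variance at baseline and at 12 months (assumed equal) and r the correlation between them. Clustering is ignored. Per patient:

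- change score: 2(1 − r)σ²
- adjusted for baseline: (1 − r²)σ²
- ratio: (1 − r²) / (2(1 − r)) = (1 + r)/2

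| assumed r | variance ratio | variance saved | SE reduction, 1 − √ratio |
|---|---|---|---|
| 0.3 | 0.65 | 35% | 19% |
| 0.5 | 0.75 | 25% | 13% |
| 0.7 | 0.85 | 15% | 8% |
| 0.9 | 0.95 | 5% | 2.5% |

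A simulation with 61 patients per arm gave ratios of 0.653, 0.748 and 0.853 at r = 0.3, 0.5 and 0.7. At r = 0.5 the gain is worth 1/0.75 = 1.33, about a third more patients.

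**3. Dependence on equal variances.** With SDs σ₀ at baseline and σ₁ at 12 months, the change-score variance minus the adjusted variance is (σ₀² + σ₁² − 2rσ₀σ₁) − σ₁²(1 − r²) = (σ₀ − rσ₁)², which is never negative. The assumption affects the size of the gain, not its direction.

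**4. Power at 61 completers per arm for a 7-point difference** (normal approximation, no clustering):

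| assumed r | SD 14 of the score: change | SD 14 of the score: adjusted | SD 14 of the change: change | SD 14 of the change: adjusted |
|---|---|---|---|---|
| 0.3 | 64.6% | 82.5% | 78.9% | 92.9% |
| 0.5 | 78.9% | 89.0% | 78.9% | 89.0% |
| 0.7 | 94.6% | 97.2% | 78.9% | 85.0% |

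**5. Whether a change outcome rules out adjustment.** It does not. With baseline as a covariate, moving from the 12-month score to the change as response alters only the baseline coefficient, by −1. In the simulation the treatment estimates were identical.

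**The case against.** The strongest reply is that no sentence says baseline will be left out. The quoted sentence defines an outcome variable, not a model. A change outcome is compatible with baseline as covariate (step 5), and the planned mixed model could already contain it. The statistical methods section is plainly not a full covariate list, since it omits treatment expectancy, which the article promises elsewhere to use. An article condenses its protocol, and covariate details are commonly left to the full protocol or the SAP, neither of which is at hand.

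Most of this stands. A reader might infer that the trial has decided on an unadjusted analysis of raw change; the article does not support that. What remains is that it positively fixes the outcomes as change, names one adjustment variable that is not the baseline value, and words the primary endpoint differently in the abstract. Followed as written, this gives the less precise of two valid analyses.

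Three further inferences also go too far:

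- **Bias.** A comparison of change is unbiased on average under randomisation. A chance baseline difference shifts it only conditionally, through regression to the mean.
- **QALYs.** The Secondary outcomes section names a difference in QALYs as an outcome and does not say how it is estimated, so it cannot be called unadjusted.
- **Power.** The unadjusted 78.9% is about one point below target. If 14 is the SD of change, the trial was already sized for a change comparison and adjustment is a bonus, not a repair.

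**Conclusion.** The point holds as an improvement in precision, not as an error that invalidates the analysis. The outcomes are defined as change, no adjustment for baseline is stated, and the data needed for it are collected. Adjustment would reduce the variance of the primary effect by 35%, 25% or 15% at r = 0.3, 0.5 or 0.7.

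A reader might take 15–35% as a known loss. It is not: it is a variance figure, it applies only if the analysis really is an unadjusted comparison of change, and it rests on an assumed r that the article does not give. The gain shrinks as r rises. A small-group variance component that adjustment does not remove would be added to both estimators and bring the ratio closer to 1.

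**What to change.** In Statistical methods {20a}, state that the primary estimate is the between-arm difference in CES-D at 12 months, from the linear mixed model with baseline CES-D as covariate, or from a model with baseline in the response and one common baseline mean for both arms. Keep the small-group structure already planned. Say the same for each continuous secondary outcome, using its own baseline value.

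Align the abstract with the Primary outcomes section so that both describe this 12-month contrast. Reporting it as an adjusted difference in change is equally acceptable, since the estimate is the same.

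Adjusting the QALY difference for baseline AQoL-8D utility is a sensible addition.

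The cost is analysis wording only, with no new data. It should be fixed before the data are analysed. If the full protocol or SAP already specifies it, one sentence in the article closes the point.
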